### Pilot study

A pilot study to test the feasibility of the Positive Outlook program and to provide both formative and process evaluation was conducted in June 2012. Twelve participants were recruited from the target population for this pilot study through the Western Australian AIDS Council. Ten participants completed baseline assessments and were enrolled to participate in the seven week Positive Outlook program. One participant withdrew in week five due to personal issues. Data was collected from the remaining nine participants immediately following the intervention. Six of the nine participants were also interviewed about their experience of using the online program. Minor adjustments were made to the content and delivery of the intervention based on the results of the pilot study.

A second pilot study was launched on the 22^nd^ October, 2012. This pilot group was intended to be the first of the RCT, however it was decided that a few additional changes were required to improve the program prior to trial. Participants completed baseline data and were randomised into the intervention (n = 19) or the control group (n = 17). Two participants withdrew in week three. Data was collected from 21 participants at the conclusion of the intervention. The findings of the pilot studies will be reported elsewhere. Participation on the discussion boards was extremely limited for the intervention group. Engagement with the Action Plans was also limited. After discussions with the facilitators of the program, interviews with the participants themselves and discussion with the intervention team, we decided to include a “live chat” into future versions of the program. We believed that the program was too flexible and the delay in responses was acting as a barrier for participation for many of the participants. By facilitating a live chat, participants will have more accountability for participation and will potentially get more out of instant responses and the “virtual” conversation whilst still maintaining their anonymity.

### Identification and recruitment of participants

Potential participants will contact the researcher directly in response to advertisements on Facebook, community organisation websites, advertisements in gay press, flyers and posters located in AIDS councils and other services for PLHIV, and GP offices and referral from health professionals. Potential participants will be directed to the Positive Outlook website (http://www.positiveoutlook.org.au) where they can register their interest by providing their name and email address on a secure server. Within one day, participants will be invited to join the study by the primary researcher (TM) and sent the electronic information and consent forms. Contamination of research participants is unlikely given the web-based nature of the intervention and use of individual login names and passwords. The primary researcher will ensure there is no double up of email addresses and postal addresses (where provided). Participants will also be recruited using multiple organisations, further reducing the chance of contamination of research participants.

### Inclusion and exclusion criteria

Inclusion criteria for participating in this study is as follows:

• HIV positive men over 18 years living in Australia

• Self identifies as gay, homosexual or MSM (men who have sex with men)

• Ability to read and write in English

• Self reported access to a computer and the internet for at least 90 minutes per week for seven weeks

• Adequate computer skills to enable participation.

### Randomisation

Participants who indicate consent will be allocated a unique participant identification number. Once sufficient participants are recruited for the first round of randomisation (n = 30), participants will be sent electronic baseline questionnaires and a registration form and be randomised to either the intervention or control condition. Participants will be allocated into either the control group or the intervention group using a computer generated list of random numbers [52]. A spreadsheet containing the participant’s unique identification numbers will be constructed. An associate researcher will allocate participants to the intervention or control group using the list of computer-generated numbers on the spreadsheet. The primary researcher (TM) is blinded to randomisation. Once randomisation has been completed, the primary researcher will email each participant advising them of their group allocation.

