**Week 6**	HIV, You and Others: Managing risk	Risks within intimate relationships
**Week 7**	Wrapping up: Review	Medication’s; Open discussion; Program review

Each group is facilitated by two peer support officers recruited from community organizations supporting PLHIV in Australia. Each facilitator receives a training session and an instruction manual describing their responsibilities. Facilitators use pseudonyms and do not have access to participants’ personal information. The facilitators are responsible for modeling desirable participation; facilitating and encouraging group discussion; moderating content on discussion boards; providing additional information; sending participants reminders where required via personal messages tab and providing feedback regarding participants goal setting and action planning activities. The facilitators also monitor and facilitate the weekly “live chat.” There is no predetermined timeframe for the facilitators to spend on the program, however, they are asked to commit a minimum of 30 to 45 minutes per day and up to two hours when facilitating the “live chat”. Participants are able to communicate directly and privately with the facilitators if required through a ‘private messages’ option on the website. Participants also receive weekly reminders of the program delivered via email and or SMS from an external facilitator (the primary researcher).

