### Data collection

#### Quantitative data

Data will be collected online (via Survey Monkey) with the exception of the SF-12^®^ which the primary researcher (TM) will deliver via post or phone. Electronic questionnaires will be emailed to participants at three time points: baseline (Timepoint 1); immediately after the completion of the intervention or eight weeks post randomisation (Timepoint 2); and 12 weeks following the intervention (Timepoint 3). Demographic information will be collected at time one only and will include age, year of diagnosis, co existing conditions, relationship status, living situation and annual income. It is anticipated that data collection at each timepoint will take no longer than 45 minutes to complete. Participants will be given two weeks to submit completed follow up questionnaires. They will receive email, SMS and phone reminders as required. For a detailed flow chart on data collection, please see Figure 1.

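### The statement that the primary researcher is blinded can describe allocation concealment at most; any follow-up SF-12 taken by phone is taken by the unblinded programme developer

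*Protocol article*

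**What the plan says.** The relevant statements are spread over three parts of the protocol article.

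- **Randomisation.** Allocation is done by a colleague: "An associate researcher will allocate participants to the intervention or control group using the list of computer-generated numbers on the spreadsheet". Of the primary researcher, the section says that this person "is blinded to randomisation. Once randomisation has been completed, the primary researcher will email each participant advising them of their group allocation".
- **The positive outlook intervention.** The primary researcher developed the programme with an intervention team. Two peer support officers run each group. In addition, participants get "weekly reminders of the program delivered via email and or SMS from an external facilitator (the primary researcher").
- **Data collection, Quantitative data.** The general rule is "Data will be collected online (via Survey Monkey) with the exception of the" SF-12. That questionnaire is the one that the primary researcher "will deliver via post or phone". Assessments take place at baseline (Timepoint 1), after the intervention or eight weeks after randomisation (Timepoint 2), and 12 weeks after the intervention (Timepoint 3).

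The SF-12 is listed under secondary outcome measures. The three primary measures are the PROQOL-HIV, the heiQ and the Positive Outlook Self-efficacy Scale.

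**The concern.** A statement of blinding tells the reader that someone's knowledge of the allocation cannot influence the data. Here it is attached to the person who announces every allocation and later delivers an outcome questionnaire. If that questionnaire is read out over the phone, the answers pass through someone who knows the arm and built the programme. Men in the programme may give more favourable answers to that person, and the caller may, without intending it, prompt or record differently.

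Participants cannot be blinded to an online group programme. Neutral and uniform collection is therefore one of the few protections left for self-reported outcomes. For the SF-12, the plan as written does not secure it. Allowing two modes adds a second route to bias: if the phone is used more in one arm than in the other, an ordinary difference between spoken and written answers becomes a difference between arms.

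**Working it through.** The plan gives no figure on this point, so the check is a comparison of the statements in time order.

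1. **While a round is being allocated.** The associate researcher allocates from the computer-generated list. The primary researcher may well not know the sequence. The blinding statement can be true here.
2. **When allocation is announced.** The primary researcher emails each man his group, and so knows every assignment from this point on.
3. **During the seven weeks.** The primary researcher sends weekly programme reminders. The article describes these as part of the intervention. Sending them only to men in the programme, which is the natural reading, again requires knowing who is in it.
4. **Timepoints 2 and 3.** The primary researcher delivers the SF-12 by post or phone. Both time points come after step 2, so this person is unblinded at both. Nothing in the article hands follow-up calls to someone else.

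**Reach.**
- Instruments: 3 primary + 4 secondary (SF-12, DASS, DSSI, MAH) = 7. Six are completed online; 7 − 6 = 1 goes through the primary researcher.
- Time points: 3 in all. Baseline questionnaires belong to the randomisation step and may precede the announcement, so 3 − 1 = 2 are clearly exposed.
- Mode: a posted form is self-completed. Only phoned forms carry the interviewer risk.

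**Form of the bias.** Let p be the share of men phoned at a follow-up, and b the average shift in a score from being phoned by this researcher. Let I and C mark the intervention and control arms. The arm difference then moves by

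p_I × b_I − p_C × b_C.

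- If nobody is phoned, p_I = p_C = 0 and the term is zero.
- If the shares are equal (p) but the caller's influence differs, the term is p × (b_I − b_C).
- If the influence is equal (b) but the shares differ, the term is b × (p_I − p_C).

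The documents give neither p nor b for either arm, so no value can be calculated. The difference of 11 with standard deviation 19.8 under Sample size calculations concerns self-efficacy and is no yardstick for the SF-12. Adjusting for baseline in the planned ANCOVA does not remove a shift that arises after allocation is known.

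**The case against.** The strongest reply is that the Randomisation section runs in time order: a colleague allocates, the primary researcher is kept out of it, and only afterwards does that researcher announce the result. On this reading the two sentences agree, and the article never claims blinded outcome assessment. This stands. A reader might infer a flat contradiction, or an untrue claim of blinding; the text does not support that. What remains is that the article does not limit its statement to the allocation step, and that this reading leaves SF-12 collection just as unblinded.

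Other points in the plan's favour:

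- **The contact is thin.** The weekly contact is by email or SMS, and chat and feedback are run by peer facilitators. Control men also deal with the same researcher over invitation, allocation and the SF-12. This stands, and it limits how large b_I − b_C is likely to be.
- **Men know their own group anyway.** Self-report bias would remain whoever delivers the form. True, but that is no reason to add a second, avoidable source.
- **An article condenses.** The rule for who is posted a form and who is phoned may be in the full protocol, and its absence is no fault here. The article does, however, positively fix the collector and allow both modes.

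A reader might also infer that chasing of late questionnaires differs by arm, because men "They will receive email, SMS and phone reminders as required". The documents do not support this. The sentence follows a two-week window common to all men, makes no distinction by arm and does not say who makes the calls.

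**Conclusion.** The point holds in a limited form. The blinding statement can be true only up to the announcement of each round's allocation. After that the primary researcher is unblinded, and any SF-12 phoned at Timepoint 2 or 3 is taken by the programme's developer, in a mode that may vary between men and arms.

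This should be corrected, but it does not threaten the main comparison. It would be wrong to infer that the primary outcomes are collected by an unblinded assessor: all three are self-completed online. The weakness touches the eight subscales of one secondary measure, and only where the form is phoned.

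The conclusion assumes that at least some follow-up forms are phoned and that delivery by phone means the researcher asks the questions. The size of any bias is unknown; it is nil if all follow-up forms are posted and self-completed.

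**What to change.** 1. **Reword the Randomisation section.** State that allocation was concealed from the primary researcher until each round had been assigned, and that this researcher is unblinded from then on.
2. **Use one self-completed mode for the SF-12**, the same in both arms and at all three time points.
3. **If a call cannot be avoided**, use a script identical in both arms, record the mode for every form, report the share phoned by arm and time point, and add a sensitivity analysis without phoned forms. That analysis is supportive only, since the men who need a call may differ from the rest. Do not describe the associate researcher as a blinded caller, because that person performs the allocation.

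The cost is a change of wording and a fixed mode for one questionnaire. The downside is that some SF-12 forms may come back late or not at all. If the chosen mode is post, the loss would fall mainly on men who give no postal address; the recruitment section indicates that an address is not always provided.

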### The positive outlook intervention

The Positive Outlook program was developed by the primary researcher (TM) in consultation with an intervention team. The intervention team brought together people with expertise in HIV and self-management of chronic conditions. They provided feedback and recommendations to develop and refine the intervention.

The program is based on Bandura’s self-efficacy theory [18] and utilizes a self-management approach to enhance participants’ skills, confidence and abilities to manage the psychosocial aspects of HIV in their daily lives. The intervention encourages participants to take responsibility for the self-management of their condition including managing physical, social and emotional aspects of health and making behavioral changes.

The program is delivered as a closed group with approximately 15 people per group. Over seven weeks, participants log onto the intervention for approximately 90 minutes per week. The program is accessible through a website (http://www.positiveoutlook.org.au) which is password protected and consists of a series of information modules (comprised of 15–20 web pages) to be completed by the participants each week. Each module provides interactive self-management information as determined by the objectives identified in the needs assessment (See Table 1). Participants are required to complete a number of goal setting and action planning activities and to use discussion boards to communicate with other group members about their action plans, experiences, problems, progress and goal attainment. The discussion board also provides the opportunity for social support, modeling and group persuasion to occur; vital components of self-management and self-efficacy theory [17,37]. The program also contains a “live chat” feature whereby once a week at a designated time, participants are encouraged to log on simultaneously to discuss the week’s content.

**Table 1 T1:** Program overview

	**Topic**	**Chat topic**
**Week 1**	Part 1: Orientation	Introductions and program expectations; Health goals.
	Part 2: Maintaining a healthy lifestyle	
**Week 2**	HIV and You: Emotional well being and social connectedness	Stress management and depression
**Week 3**	Talking About HIV: Disclosure of positive status to friends and family	Disclosure
**Week 4**	HIV, You and Others: HIV and intimate relationships; safe sex basics	Relationships
**Week 5**	HIV, You and Others: Disclosure to partners	Disclosure to intimate partners

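### The primary researcher is described as blinded with no time limit, yet knows every allocation once a round is randomised and then delivers the SF-12 by post or phone

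*Protocol article*

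**What the plan says.** The protocol article gives the primary researcher several roles, in different sections.

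- **Randomisation.** The list is worked by someone else: "An associate researcher will allocate participants to the intervention or control group using the list of computer-generated numbers on the spreadsheet". The primary researcher, by contrast, "is blinded to randomisation. Once randomisation has been completed, the primary researcher will email each participant advising them of their group allocation".
- **The positive outlook intervention.** "The Positive Outlook program was developed by the primary researcher", with an intervention team. During the seven weeks participants receive "weekly reminders of the program delivered via email and or SMS from an external facilitator (the primary researcher"; the bracket identifies the sender as the same person.
- **Quantitative data.** All questionnaires are completed online except the SF-12, which the primary researcher "will deliver via post or phone". On late follow-up questionnaires, the section says of participants: "They will receive email, SMS and phone reminders as required". It does not say who sends these.
- **Qualitative data.** The primary researcher also keeps field notes throughout the trial.

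The objectives and the outcome sections place the SF-12 among the secondary outcomes. The primary outcomes are the PROQOL-HIV, the heiQ and the Positive Outlook Self-efficacy Scale.

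**The concern.** The word used is blinded, and no end point is attached to it. Someone appraising the trial could credit it with a blinded follow-up contact, when the person concerned has told every man his group and has written weekly to those in the programme.

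What is at stake is the SF-12. A man who answers it by phone does so to the person who developed the programme, knows his arm and, if he is in the programme arm, has been in weekly contact with him. That leaves room for the interviewer's expectations to colour how questions are put or probed, and for courtesy answers in one arm more than the other. Either would appear as a group difference on a health and quality-of-life score. This bias is avoidable, and it comes on top of the self-report bias that any usual-care comparison carries because the men know their own arm.

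**Working it through.** No figure in the plan states this point, so the check is mainly of the text, in time order.

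1. **Before and during a round's randomisation.** An associate researcher allocates from a computer-generated list against identification numbers. The primary researcher has no stated part in this. Concealment is consistent with the text here.
2. **Straight after randomisation.** The primary researcher emails each man his group. From this moment this person knows every allocation in the round.
3. **Weeks 1 to 7.** The same person sends the weekly reminders. They are described as part of the programme, so I take the recipients to be the programme arm. Knowledge of arm is refreshed each week.
4. **Timepoint 2 (end of the intervention or eight weeks after randomisation) and Timepoint 3 (12 weeks after the intervention).** The same person delivers the SF-12. The sentence that lists the timepoints refers to electronic questionnaires, so SF-12 administration at each timepoint is an inference, though a natural one for an outcome measure. A baseline SF-12 completed before randomisation is not exposed.
5. **By mode.** A posted form is self-completed and involves no interviewer. A phoned form does. The share taken by phone is not given.
6. **By outcome.** The three primary scales are filled in online. The interviewer route does not reach them.

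**Sample size.** The plan's own calculation is unaffected. A two-sided two-sample t-test with difference 11, SD 19.8, 80% power and α = 0.05 needs 51.84 men per group, which rounds up to the stated 52.

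**Illustration only; the bias sizes are assumptions with no basis in the documents.** Suppose there is no true effect, 60 men per arm (120/2, equal split, all responding), a two-sided 5% t-test on one SF-12 score, and a net shift of b standard deviations in favour of the programme arm. The rejection probability comes from the noncentral t with noncentrality b × √(n/2) = b × √30 = 5.48b.

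| b (SD) | noncentrality | false-positive rate |
|---|---|---|
| 0.1 | 0.55 | 8.4% |
| 0.2 | 1.10 | 19.2% |
| 0.3 | 1.64 | 37.1% |

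If only a share p of men in each arm is phoned and the shift among them is d, then b = p × d. With every form posted, p = 0 and this route adds nothing to the nominal 5%. The table shows the direction of the effect, not its size in this trial. It is also simpler than the planned baseline-adjusted ANCOVA, and the SF-12 has eight subscales. The planned standardised effect (11/19.8 = 0.56) belongs to a self-efficacy scale and is no benchmark for the SF-12.

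**The case against.** The strongest reply is that the sentence concerns randomisation, not assessment. It stands in the Randomisation section, directly after the associate researcher's task, and the next sentence opens by saying that randomisation is over. Read as a sequence, the researcher is kept from the list while it is applied and is told afterwards, and nothing conflicts. This is a fair reading. A reader might infer that the blinding statement is simply false; the text does not prove that. It shows wording that is open-ended and too broad for what the roles allow. The fair reading still leaves the researcher aware of allocation at follow-up.

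A reader might also infer that outcome collection as a whole is compromised, or that blinded assessment was promised. Neither is supported. No section claims blinded outcome assessment, the primary scales are self-completed online, and the SF-12 may be posted.

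Nor can it be said that non-responders are chased differently by arm. The sender of the reminders is not named, and one process is described for all participants. It is a possibility that the wording leaves open, no more.

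Finally, call scripts and staffing details are commonly left to a full protocol. That is accepted. The point rests on the roles that the article does assign, not on details it omits.

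**Conclusion.** The point holds in a limited form. As worded, the blinding statement has no time limit, while the roles stated elsewhere allow only concealment until each round has been randomised. After that the primary researcher is unblinded, and any SF-12 taken by phone after randomisation is open to interviewer and courtesy bias.

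The exposure is confined to one secondary instrument and, within it, to phoned administrations. The primary outcomes are not reached by this route. The size of the bias cannot be derived from the documents, and the false-positive rates above are illustrations under assumed shifts. The conclusion rests on two inferences: that the weekly reminders go to the programme arm, and that the SF-12 is given at follow-up as well as at baseline. This is a modest, cheaply corrected weakness, not a threat to the trial's main comparison.

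**What to change.** 1. Replace the blinding sentence in the Randomisation section with: *Allocation is concealed from the primary researcher until each round has been randomised; the primary researcher is aware of allocation afterwards.*
2. Have the SF-12 self-completed in both arms at every timepoint, by post (already one of the two planned modes) or online. The recruitment section indicates that a postal address is not always provided. Where a call cannot be avoided, let an existing team member who does not know the allocation make it, with one script for both arms.
3. State that the same reminder sequence for follow-up questionnaires applies in both arms.

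Moving the allocation emails and weekly reminders to the associate researcher would not be enough by itself. The primary researcher is also named as the programme's external facilitator and keeps field notes during the trial, so could still learn who is in which arm. The associate researcher, who is described as working from identification numbers, would also need the men's contact details.

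The cost is small: one sentence changes, a mode already planned becomes the rule, and no sample-size figure moves. The downsides are possibly slightly fewer SF-12 returns without phone completion, and a blinding statement that reads less favourably but is accurate.
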